## Methods

### Participants

We will recruit 184 participants in order to create 92 dyads: 30 dyads in which a person who meets the criteria for AD with primary memory impairment [1] is paired with a caregiver, 16 dyads in which a person who meets the criteria for svPPA [4] is paired with a caregiver, and 46 pairs of healthy controls with no cognitive complaints (HC).

The dyad partners must have socialized together for at least 2 h per week for at least 5 years. Patients and HC must be aged 50–85 years. Patients’ caregivers and HC must have no cognitive complaints and a Montreal Cognitive Assessment (MoCA) [51] score > 25.

Exclusion criteria for all participants will be (1) concurrent participation in a therapeutic drug trial, (2) prior neurological disorders (stroke, epilepsy, head injury with loss of consciousness lasting more than 1 h), (3) chronic alcoholism or drug addiction, (4) a clinically severe major psychiatric disorder within the previous 10 years, and (5) use of psychotropic medication.

The size of the patient groups was determined according to the feasibility of including this type of patient, based on studies carried out for more than 15 years in our research unit [43, 52, 53]. The size of the HC group was determined in relation to the size of the patient groups. To ensure that HC are not cognitively impaired, a quick cognitive test will be performed at the beginning of the psychological interview. Individuals who perform below the normal range will be excluded from the study and replaced.

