### Data analysis plan

Each participant’s performance in the presence-only context will serve as a reference score, and a differential score will be calculated by subtracting this reference score from the participant’s memory performance in the collaboration context. The *z* score of this differential score will then be calculated, based on the mean and standard deviation for the HC group. This will show whether each patient’s differential score differs significantly from that of the HC group. The same analyses will then be carried out for performance in the observation context.

As this study is designed to identify determinants (social interactions and abilities, cognitive skills, and personality traits) that could explain the differential scores for the collaboration and observation contexts, we will carry out multiple comparative case analyses [48–50], based on the differential scores for the collaboration context of at least three patients whose memory performance is substantially better in the collaboration condition, compared with the presence only condition, and for three patients whose performance is only minimally better. These six patients will be compared on their social skills (social interactions and abilities), personality (especially the cooperation and determination dimensions), and memory performance in classic neuropsychological tests. Following a logic of replication, other patients will be added to the analyses, to see whether a regular pattern emerges. The same analyses will be conducted on differential scores for the observation context.

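### The z score treats the mean and SD of 46 controls as known values; a two-sided 5% rule then has an average error of about 5.9%, which a single-case t test corrects at almost no cost

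*Protocol article*

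**What the plan says.** In the protocol article, under Data analysis plan, each participant's presence-only score is subtracted from the score in the collaboration context. This difference is then put on a z scale; the "score of this differential score will then be calculated, based on the mean and standard deviation for the HC group". The inference follows directly: the result is meant to tell, for each patient, if the "differential score differs significantly from that of the HC group". The observation context gets the same treatment: "The same analyses will then be carried out for performance in the observation context".

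Under Participants, the patient groups are "30 dyads in which a person who meets the criteria for AD with primary memory impairment" and "16 dyads in which a person who meets the criteria for svPPA", so 46 patients, set against 46 HC pairs. On the size of the norm, the article says: "The size of the HC group was determined in relation to the size of the patient groups". It gives no precision target for the HC mean or SD, and it states no alpha, sidedness, z cut-off or multiplicity adjustment for the patient-level comparison.

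**The concern.** A z score supports a normal-theory significance statement only when its centring and scaling values are population constants. Here both are sample estimates from a few dozen people. The patient's distance from the HC mean carries the sampling error of that mean, and the denominator carries the sampling error of the SD. Ignoring both makes the reference distribution too narrow and the p-values too small, most of all in the tails.

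This affects the only significance statement in the article's analysis plan. That statement is made for each of 46 patients in two contrasts, and the Discussion aims to find the most favourable learning context for the individual patient. The same estimated norm also serves every patient, so an HC SD that is too small or too large by chance moves all the patient-level results in one direction.

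**Working it through.** **Inputs**
- Controls in the norm: n = 46, from the 46 HC pairs (Participants), with one tested participant per pair. The article does not state the latter for HC outright. It follows from the Social memory task section, where the tested participant is a patient or an HC and the other dyad member acts as partner.
- Patients: 30 + 16 = 46. Contrasts: 2, so 92 patient-level tests per memory score.
- The article gives no cut-off or alpha, so there is no stated figure to reproduce. Two-sided levels of 0.05, 0.01, 0.05/46 and 0.05/92 are assumed here to show the range.

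**Formula.** Suppose the patient and the controls come from the same normal distribution. The difference between the patient and the HC mean has variance SD² × (1 + 1/n), and the estimated SD has n − 1 df. So z / √(1 + 1/n) follows t with n − 1 df. For n = 46, √(47/46) = 1.0108 and df = 45.

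- True error of the rule |z| > c: 2 × P(t₄₅ > c / 1.0108)
- Correct cut-off on the z scale: t₄₅ quantile × 1.0108

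For the 5% rule: 1.960 / 1.0108 = 1.939, and 2 × P(t₄₅ > 1.939) = 5.88%. The correct cut-off is 2.014 × 1.0108 = 2.036.

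| Nominal level (two-sided) | Normal cut-off | True average error | Ratio | Correct cut-off |
|---|---|---|---|---|
| 5% | 1.960 | 5.88% | 1.18 | 2.036 |
| 1% | 2.576 | 1.43% | 1.43 | 2.719 |
| 0.05/46 = 0.109% | 3.267 | 0.230% | 2.12 | 3.530 |
| 0.05/92 = 0.054% | 3.458 | 0.134% | 2.46 | 3.765 |

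A simulation of 400,000 sets of 46 patients, each set sharing one HC sample, gives 5.88%, 0.230% and 0.133% at cut-offs 1.960, 3.267 and 3.458.

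**Size in patients.** At 1.96 the expected number of false flags among 46 patients is 46 × 0.0588 = 2.7, against 46 × 0.05 = 2.3 for an exact 5% test: about 0.4 more per contrast.

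**What the t test does not cure.** The HC SD estimate lies between √(χ²₄₅ 2.5% quantile / 45) = 0.794 and √(χ²₄₅ 97.5% quantile / 45) = 1.206 times the true SD in 95% of samples. Holding the HC mean at its true value, the error rate common to all patients is then:
- with cut-off 1.960: 2 × [1 − Φ(1.960 × 0.794)] = 12.0%, and 2 × [1 − Φ(1.960 × 1.206)] = 1.8%
- with cut-off 2.036: 10.6% and 1.4% in the same way

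The t test brings the average to 5%. The spread from one HC sample to another stays almost as wide.

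**Sensitivity to n.** With 92 controls (both members of each pair scored and taken as independent), the ratios fall to 1.09 at 5% and 1.49 at 0.05/46. With 23 controls, as an illustration of a restricted norm, the true error at 1.96 is 6.8%, a ratio of 1.36.

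**The case against.** **The effect at 5% is small.** This stands. The cut-off moves by 2.036 − 1.960 = 0.076 HC SD. The article gives no SD for the differential score. If it were 1 to 3 points (an assumption), the shift would be 0.08 to 0.23 points, less than the half-point step of the location score. Many patients would be classified alike under either rule.

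**The reference distribution is inferred.** The article does not say that z is compared with normal quantiles, and a full protocol or analysis plan that is not shown could specify a t reference. This limits confidence. But the article itself names the statistic and says that it will show significance, and the plain reading of that is a normal reference.

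**Case selection is unaffected.** Dividing every z by the same constant leaves the order of patients unchanged. The article selects cases as having substantially or only minimally better performance, not by a significance threshold. This stands where one norm is used for all.

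**Normality.** Both scores are bounded and discrete, so the tail figures are approximate, and the t test is exact only under the same assumption.

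A reader might infer two stronger conclusions, and neither is supported. The first is that the plan's error rate is about double its nominal value. That happens only at cut-offs such as 0.05/46, and the article sets no cut-off and no multiplicity adjustment. The second is that the 2% to 12% range of realised error is harm done by z and repaired by t. The range hardly changes under the t cut-off, and part of it lies below 5%.

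**Conclusion.** The point holds as a minor correction. The patient-level rule, read plainly, ignores the sampling error of the norm and is anti-conservative on average: about 5.9% for a two-sided 5% rule and about 1.4% for a 1% rule. These figures assume 46 tested controls, normally distributed differential scores and a normal reference for z. The excess is under one percentage point at 5%, and a twofold excess is conditional on a strict cut-off that the document does not adopt. Unadjusted testing of 46 patients is a larger source of false flags (2.3 expected per contrast even with an exact 5% test) than the excess shown here (0.4).

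**What to change.** In the Data analysis plan, replace the z test by the Crawford-Howell modified t test:

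t = (patient − HC mean) / (HC SD × √(1 + 1/n)), on n − 1 df.

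State that n is the number of controls in the norm actually applied. It is 46 if all tested controls are used, and smaller if the norm is restricted, for example by context order. Report with each result the patient's estimated percentile in the HC distribution and its 95% interval (from the noncentral t distribution). The interval is needed as well as the test, because it shows how far one HC sample leaves every patient's position uncertain.

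The cost is one sentence in the plan and about a line of code for the test, plus a short routine for the interval. No further participants or data are needed, and the thresholds become slightly stricter.

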#### Recall phase

The recall phase will take place after an interference task (completion of a questionnaire), and will consist of picture recognition and grid location recall. For the picture recognition, all 24 pictures (i.e., 12 targets and 12 distractors) will be displayed one by one in random order. For each picture, participants will have to say whether or not they saw the picture in the learning phase. For the location recall, the 12 target pictures will be displayed one by one, and participants will have to place each one in the box it occupied in the learning phase.

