#### Outcome of social memory task

For the learning phase, and for each social context, several scores will be collected: the number of trials performed before all the pairs of pictures are found, the number of clicks on each picture on the lefthand side of the screen, and on each picture in the grid. We will examine whether these scores are related to delayed recall performance, to establish whether a picture is remembered better and more accurately located if it has been seen several times.

For the picture recognition in the recall phase, we will record the numbers of correct responses (i.e., saying “yes” when the picture has previously been seen, and saying “no” when the picture has not been seen before) for each social context.

Finally, for the location recall, we will calculate an overall score for each social context. If a picture is correctly located in the grid, 1 point will be awarded, and if it is located in an adjacent box, 0.5 point will be awarded. If not, 0 point will be awarded.

We will assess whether social context influences the picture recognition and location recall scores, and use these scores to identify factors that could explain potential differences in recognition performance between social learning contexts.

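### Cases for the comparative analysis are picked on a raw gain from a bounded score, ignoring the presence-only level, so starting level can be mistaken for benefit from social context

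*Protocol article*

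**What the plan says.** All places are in the protocol article.

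- **Score.** Recall phase: "For the location recall, the 12 target pictures will be displayed one by one". Outcome of social memory task: "If a picture is correctly located in the grid, 1 point will be awarded, and if it is located in an adjacent box, 0.5 point", and nothing otherwise. Location recall therefore runs from 0 to 12. Recognition uses 24 pictures, so 0 to 24 correct. The Data analysis plan does not say which of the two is the memory performance.
- **Differential.** Data analysis plan: collaboration minus presence-only, then expressed as a z score on the mean and standard deviation of the healthy controls (HC). The same is done for observation.
- **Case selection.** Data analysis plan: at least three patients with a substantial gain "and for three patients whose performance is only minimally better". Neither group has a cut-off or a condition on the presence-only score. Further patients are added by replication.
- **Comparison.** The cases are compared on social skills, "personality (especially the cooperation and determination dimensions), and memory performance in classic neuropsychological tests".
- **Patients.** Participants: 30 with AD and 16 with svPPA. "Patients and HC must be aged 50–85 years". Caregivers and HC "must have no cognitive complaints and a Montreal Cognitive Assessment (MoCA) [51] score > 25". The article states no corresponding limit for patients.

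**The concern.** The secondary objective is to find what explains better memory in a social context, and the Discussion wants to use the answer to pick the best learning context for each patient. Both rest on the contrast between high-gain and low-gain cases.

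The size of a raw gain depends on where the patient starts. A patient who already scores near the maximum alone has no room to show a benefit. A patient with a low presence-only score has room, and part of that low score may be bad luck that does not recur in the second context. Either way, case group is tied to starting level. Classic memory tests, which are likely to track that level, are among the variables compared. A feature of the scale could thus appear as a finding about patients.

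**Working it through.** The plan states no figure on this point, so there is none to reproduce.

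**1. Ceiling (arithmetic).** Largest possible gain on location recall = 12 − presence-only score.

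| Presence-only score | Largest possible gain |
|---|---|
| 6 | 6 |
| 9 | 3 |
| 10 | 2 |
| 11 | 1 |
| 12 | 0 |

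The same holds for recognition, with 24 in place of 12.

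**2. The z score does not help.** z = (differential − HC mean) / HC SD is linear with one mean and one SD for all patients. Their ranking, and therefore who is picked, is unchanged.

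**3. Floor (arithmetic, grid layout assumed).** With half a point for an adjacent box, the expected score from pure guessing on 12 boxes is (12 + 0.5 × ordered adjacent pairs) / 12.

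- 3×4 grid, boxes sharing a side: (12 + 0.5 × 34) / 12 = 2.42
- 2×6 grid, boxes sharing a side: (12 + 0.5 × 32) / 12 = 2.33
- 3×4 grid with diagonals: (12 + 0.5 × 58) / 12 = 3.42

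So the floor is about 2 to 3 points, not 0. Under guessing in both contexts the differential has an SD of about 1.5 to 1.6. A differential of 0 to 1 has probability about 0.35, and one of 3 or more about 0.04. A floor patient can fall in either group.

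**4. Same response, different expected gain.** Assume a picture is remembered with probability p, otherwise guessed with expected credit 2.42/12 = 0.20, and that the social context adds 0.8 on the logit scale for every patient. The expected gain is 12 × 0.80 × [expit(logit p + 0.8) − p].

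| p alone | 12 × change in p | Expected gain (× 0.80) |
|---|---|---|
| 0.05 | 0.66 | 0.53 |
| 0.40 | 2.37 | 1.90 |
| 0.95 | 0.32 | 0.26 |

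Below the ceiling, chance variation in the differential is as large as these expected gains. Selecting the extremes therefore partly selects on noise.

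**5. Simulated selection, identical response for all.** Inputs: 30 AD and 16 svPPA patients (Participants) and the article's scoring. Assumed: 3×4 grid, the same +0.8 for everyone, normal ability on the logit scale with SD 1, and selection of the three largest and the three smallest non-negative gains.

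| Assumed mean ability (AD / svPPA) | Mean presence-only score, low-gain vs high-gain | Share at 10 or more: low-gain / high-gain / all patients |
|---|---|---|
| −1.5 / +1.5 | 8.6 vs 3.8 | 54% / 0% / 23% |
| −2 / 0 | 5.7 vs 3.6 | 14% / 0% / 7% |

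In the first setting svPPA patients made up 57% of low-gain and 18% of high-gain cases, although diagnosis had no effect on response. Across a wider set of assumed distributions, mean presence-only scores were 4.1 to 9.2 in low-gain against 3.0 to 4.4 in high-gain cases. Presence-only scores of 10 or more occurred in 1% to 57% against 0%. Low scorers were more common among high-gain cases (28% to 60%) than among low-gain cases (5% to 37%).

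**6. Simulated selection, response varying independently of ability.** Assumed: 46 patients, logit gains with mean 0.8 and SD 0.8, and low-gain cases with a differential above 0. The difference in mean ability, high-gain minus low-gain, ran from −1.05 to +0.90 SD over the ability distributions tried. It was near zero in some (0.07, 0.08, 0.03).

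**The case against.** **Size is not knowable from the article.** This stands. No score distribution is given, and the ranges above are wide because of it. The Background calls severe learning deficits a core feature of AD, so presence-only scores near the maximum are less plausible in the 30 AD patients. The ceiling problem may be mainly one for svPPA, where language is the predominant deficit and the task is nonverbal.

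**The task and the analysis may already guard against it.** The task is adapted to patients, and boxes are blocked so that it is not too simple. The Discussion speaks of profiles for each target population, which points to analysis by diagnosis. If cases are chosen within diagnosis, the AD-versus-svPPA part falls away. The part about starting level within a diagnosis does not.

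**A severity limit may exist elsewhere.** This is a condensed article, and the full protocol may restrict severity. The point does not depend on it: what is at issue is the selection rule, which the article does state.

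**Memory level is examined openly, and replication would expose an artefact.** Comparing memory tests does not help, since that is where the artefact would show. Replication adds patients under the same rule.

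**Stronger readings that a reader might infer.** One is that very impaired patients will be classed as low gainers. The calculation does not support this: in most settings patients near chance were more common among high-gain cases. Another is that the contrast measures disease stage and not response. That goes too far: the ability difference takes either sign, is sometimes near zero, and can reflect diagnosis instead of stage.

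**Conclusion.** The point holds as a risk of confounding. A patient near the maximum cannot be a high-gain case, by arithmetic alone, and low presence-only scores are favoured among high-gain cases through noise. With every patient responding identically, the rule still produced groups that differed in starting level in the settings above. Presence-only scores of 10 or more occurred in about 1% to 57% of low-gain cases and in no high-gain cases.

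These shares rest on an assumed grid layout, assumed score distributions and location recall as the outcome. Only the bound and the linearity of the z score are free of such assumptions. The documents do not show that the problem will be frequent, nor that the case contrast is uninformative about response to social context. The rule should still be changed, because the secondary objective rests on it and the data needed are already collected.

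**What to change.** In the Data analysis plan, amend the case-selection rule:

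1. Name the recall score used and give the gain that counts as substantial.
2. Do not admit as a low-gain case a patient whose presence-only score leaves less room than that gain. For illustration only: if the gain were 3 points on location recall, presence-only scores above 9 would be set aside.
3. Report those patients separately as not classifiable for that contrast, together with patients at chance in both contexts (about 2 to 3 of 12 on location recall, to be computed from the actual grid; 12 of 24 on recognition).
4. Choose high-gain and low-gain cases with similar presence-only scores, within the same diagnosis where such patients are available. Apply the same rule to patients added by replication and to the observation contrast.

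Do not also require matching on MoCA. Cognitive skills are among the determinants under study, and that match would remove much of the contrast the study wants to examine.

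The cost is a change of wording with no new data. The downside is fewer candidate cases, possibly mainly among the 16 svPPA patients, so close matches may not always be found.

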## Discussion

Given that individuals with neurodegenerative diseases may need to learn new information despite their cognitive disorders, establishing whether social interaction favours this learning could lead to the development of new cognitive rehabilitation techniques. The purpose of the present study will therefore be to find out whether a particular social context can improve the memory performance of patients with neurodegenerative diseases, and shed light on cognitive, social and personality variables that could subtend differences in memory performance between social learning contexts (i.e., collaboration or observation vs. presence-only).

As this is a multiple comparative case study, cognitive, social and personality profiles will be established for each target population, in order to identify the most beneficial learning context for each patient. Depending on the patient’s profile, strategies can then be devised to compensate for cognitive deficits.

The MEM&SO protocol will therefore have both theoretical and practical implications in the field of social cognition, bringing social psychology concepts to neuropsychology.

## Data Availability

Not applicable.

## Abbreviations

MEM&SO: Memory and social interactions in neurodegenerative disease
AD: Alzheimer disease
svPPA: Semantic variant of primary progressive aphasia
ToM: Theory of mind
HC: Healthy control
MoCA: Montreal cognitive assessment
